## 5.1 Pre-Study Screening Tests and Safety Assessment

### 5.1.1 Pre-Study Screening Tests

Pre-study screening tests must be performed according the following time frames:

Within 4 weeks: tumor assessments based on contrast CT of chest and abdomen and/or PET/CT

Within 2 weeks: medical history, physical exam, vital signs, height, weight, ECOG, evaluation of symptoms and medications, clinical chemistry, hematology, LDH.

Within 1 week: pregnancy test for women of child-bearing potential.

### 5.1.2 Safety Assessment

The safety of CPI-613 will be assessed from the first dose to 1 month after last dose of CPI-613. The assessment will be based on:

- evaluation of symptoms

- vital signs

- ECOG performance status and survival

- clinical chemistry

- renal function

- hematology

The specifics of the safety tests are described in Section 5.2. All safety assessment tests are performed during screening (performed within 2 weeks prior to Cycle 1 treatment with CPI-613. Symptom evaluation and vital signs should be performed prior to each administration of CPI-613. ECOG performance status, clinical chemistries, renal function, and hematology should be performed on day 1 of weeks 1, 2, and 3 for each treatment cycle, with results available for review within 24 hours before administration on day 1 of study drug administration.

###

### 5.1.3 Tumor Assessment

Tumor response will be assessed based on RR, and PFS, derived from contrast CT of chest and abdomen and/or PET/CT at baseline and after every two cycles. Contrast CT and/or PET/CT should be performed during week 4, preferably on Wednesday or later (days 3, 4 or 5). RR is the primary endpoint, whereas PFS and OS are secondary endpoints.

According to the Response Evaluation Criteria in Solid Tumors (RECIST), the efficacy of treatment for solid tumors is determined by the tumor size. RECIST criteria are the golden standard to evaluate the tumor. In this study RECIST criteria will be used to evaluate response. However, there is a *pseudoprogression* phenomenon described with the use of CPI-613 in Phase I solid tumor studies (Lee et al. 2012).

It is felt that if CPI-613-induces necrosis of the tumor lesion there may be some radiographic evidence for increasing size. CPI-613 induces tumor necrosis due to its mechanism of action – selectively targeting the altered form of mitochondrial energy metabolism in tumor cells, causing changes in mitochondrial enzyme activities and redox status, which leads to apoptosis, necrosis, and autophagy of tumor cells (Lee et al., 2011; Lee et al., 2012; Senzer et al., 2012; Zachar et al., 2011; Retter et al., 2012).

For the purposes of this study, pseudoprogression will be defined and considered in patients who meet RECIST criteria of progression. It will be the treating physician’s discretion to continue treatment in this situation if the patience is deemed to be getting clinical palliative benefit. In these patients, the study drug can be given for another two cycles prior to making definitive determination of progression or response.

OS will be determined from the first dose of CPI-613 to death, assessed until patient death..Post-study survival, medical and cancer treatment information will be collected bimonthly via telephone contact after treatment termination.

RR is defined as % of patients who experienced a complete response (CR) or partial response (PR). CR and PR are based on Response Evaluation Criteria in Solid Tumor (RECIST) Version 1.1 (Eisenhauer et al. 2009). The best response recorded from the start of the treatment until disease progression (DP) will be considered.

PFS will be determined from the first dose of CPI-613 to DP or death due to any cause.

*5.1.4 Use of pre-study data for analyses*

The following pre-study tests and evaluations should be documented for future data analysis: ECOG, LDH, and CT (or PET/CT) data.

Pre-study ECOG scores and LDH values will be transferred to the Oncology Research Information System (ORIS) database at the time of registration. All subsequent ECOG scores and LDH values should be recorded on the Efficacy Assessment Form (Appendix D), which will be entered into the corresponding REDCap database. CT or PET/CT data will be recorded on the Measurement Form (Appendix G).

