**Proprietary and Confidential**

# SCHEMA

Histologic Diagnosis of Relapsed or Refractory Small Cell Lung Cancer (SCLC) Post-1st line chemotherapy

Response/Stable Disease/Clinical Benefit

Continue until clear disease progression.

Informed consent

Treatment with 2 cycles of CPI-613

Cycle length: 4 weeks

Treatment given on days 1 and 4 of weeks 1 through 3

Radiographic surveillance

Scan performed during week 4 of cycle 2, 4, 6 and every 2 cycles thereafter

No Response

Discontinue treatment

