## 6.1 Sample Size, Dose Levels and Justification of the Dose

The sample size will be 20 for this pilot trial.

This study will use the maximum tolerated dose (MTD) established in the study conducted by Pardee and colleagues (CCCWFU 29109; IRB00012124). This MTD for single-agent use of CPI-613 infused over 2 hours is 3,000 mg/m^2^.

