# 9.0 STATISTICAL CONSIDERATIONS

This is a pilot study with the primary goal to be able to determine initial estimates of response rate (RR), and secondary goals to determine progression-free survival (PFS) and overall survival (OS). Data from this trial will also provide additional data concerning the safety profile of the CPI-613 therapy. We now describe anticipated accrual rates, proposed analyses, and sample size considerations.

Accrual Rate

We anticipate accruing one to two patients per month for this protocol. Thus, we anticipate that we will reach the target sample size of 20 patients treated at MTD within eighteen months.

Proposed Analyses

The analyses for this protocol will be primarily descriptive. With a sample size of 20 treated at MTD, we will be able to get initial estimates of RR, PFS, OS, and safety and toxicity.

For the primary outcome of tumor response rate we will present the proportion of patients who are CR, PR, SD or PD (Complete response, Partial response, stable disease and progressive disease, respectively). In addition, we will estimate the proportion of responders as the percent of patients who are SD, PR and CR, as well as RR (sum of PR + CR) and Disease Control Rate (DCR, which is the sum of SD, PR and CR). For these rates we will also include 95% confidence intervals.

For the time-to-event outcomes, we will estimate survival curves for OS and PFS using Kaplan-Meier techniques. In addition, we will estimate the 6 month and 1-year OS and PFS rates for these participants. We will estimate median overall and progression free survivals for these patients as well. We will also examine safety and toxicities for these 20 patients by looking at each toxicity identified earlier in the protocol by grade.

Sample Size Considerations

Since this is a single arm pilot study, our primary goal is to gather preliminary data on response rates and not to test a specific hypothesis per se. With this sample size we will be able to estimate the response rate using a 2-sided 95% confidence interval with an interval that will extend no more than 0.21 from the observed response rate (if we conservatively assume a response rate of 0.5 for calculations).

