# APPENDIX C – CCCWFU ADVERSE EVENT LOG

# *Only Grade 3 OR higher Need to be recorded*

# APPENDIX D – Data Collection Form for Efficacy Assessment

**ORIS PID:** _______________________ **Date Completed:** ____ / ____ / ____

**Visit:**  Pre-study  Cycle 1 Visit  Cycle 2 Visit  Cycle 3 Visit  Cycle 4 Visit

Cycle 5 Visit  Cycle 6 Visit  Cycle 7 Visit  Cycle 8 Visit  Cycle 9 Visit

Cycle 10 Visit  Other (Specify: _________________________________)

**ECOG Performance Status (Date Performed:** ____ / ____ / ____)

0 Fully active, able to carry on all pre-disease performance without restriction.

1 Restricted in physically strenuous activity but ambulatory and able to carry out work of a light or sedentary nature, e.g., light house work, office work.

2 Ambulatory and capable of all self-care but unable to carry out any work activities. Up and about more than 50% of waking hours.

3 Capable of only limited self-care. Confined to bed or chair more than 50% of waking hours.

4 Completely disabled. Cannot carry on any self-care. Totally confined to bed or chair.

**Date of contrast CT (chest / abdomen) and/or PET/CT**: ____ / ____ / ____

**Were new lesions identified on contrast CT (chest / abdomen) and/or PET/CT?**  Yes  No

**Has this subject progressed according to RECIST criteria? (As determined by the treating physician)**  Yes  No

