**(Specify)**

| Date of Observation (mm/dd/yy) | |  |  |  |  |  |  |
| --- | --- | --- | --- | --- | --- | --- | --- |
| Cycle: | |  |  |  |  |  |  |
| **TARGET LESIONS** | |  |  |  |  |  |  |
| Response Status (CR, PR, SD, PD) | |  |  |  |  |  |  |
| List sites for response: | Means of Evaluation | Measurement | Measurement | Measurement | Measurement | Measurement | Measurement |
| 1. |  |  |  |  |  |  |  |
| 2. |  |  |  |  |  |  |  |
| 3. |  |  |  |  |  |  |  |
| 4. |  |  |  |  |  |  |  |
| 5. |  |  |  |  |  |  |  |
| 6. |  |  |  |  |  |  |  |
| 7. |  |  |  |  |  |  |  |
| 8. |  |  |  |  |  |  |  |
| 9. |  |  |  |  |  |  |  |
| 10. |  |  |  |  |  |  |  |
| Total sum of LD for all Target Lesions: | |  |  |  |  |  |  |
| **NON-TARGET LESIONS** | | | | | | | |
| Response Status  (CR, Incomplete Response/SD, PD): | |  |  |  |  |  |  |
| List sites for response | Means of Evaluation | Measurement | Measurement | Measurement | Measurement | Measurement | Measurement |
| 1. |  |  |  |  |  |  |  |
| 2. |  |  |  |  |  |  |  |
| 3. |  |  |  |  |  |  |  |
| 4. |  |  |  |  |  |  |  |
| 5. |  |  |  |  |  |  |  |
| 6. |  |  |  |  |  |  |  |
| 7. |  |  |  |  |  |  |  |
| **Observer Signature:** | |  | | | | | |

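### The primary response rate rests on the best recorded response with no stated confirmation, so one unconfirmed CR or PR reading makes a responder

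*Protocol*

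**What the plan says.** Section 2.2 names RR as the primary outcome. Section 5.1.3 defines it as the percentage of patients with CR or PR, bases CR and PR on RECIST version 1.1 by citation, and gives the rule for repeated assessments: "The best response recorded from the start of the treatment until disease progression (DP) will be considered".

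Imaging follows a fixed schedule. The Schema reads: "Scan performed during week 4 of cycle 2, 4, 6 and every 2 cycles thereafter". With 4-week cycles, that is one scan every 8 weeks.

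The only confirmation mentioned concerns progression. Section 6.3 refers to progression confirmed after two further cycles, and Section 5.1.3 allows a second look in patients who already meet RECIST progression. Neither covers a patient first read as CR or PR.

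Two forms carry the tumour data:
- Appendix D asks about new lesions and then "Has this subject progressed according to RECIST criteria? (As determined by the treating physician". It has no entry for response.
- Appendix G has separate status rows for target and non-target disease and a line for "Total sum of LD for all Target Lesions". It has no entry for overall response, best response or confirmation.

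On size and purpose, Section 6.1 states: "The sample size will be 20 for this pilot trial". Section 9.0 aims to "estimate the response rate using a 2-sided 95% confidence interval".

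**The concern.** Read plainly, the best-response sentence lets a single scan read as PR settle a patient's classification, even if the next scan does not support it. Reading error on a borderline change can go either way. A rule that keeps the best of several readings tends to retain the favourable errors and discard the unfavourable ones. Here the readers know the treatment, no independent read is mentioned, and there is no control arm in which the same error would appear.

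An initial estimate of RR is the trial's stated primary goal. If unconfirmed readings are mixed in without being identified, a later reader cannot tell how much of the estimate reflects responses that lasted to a second scan. The forms add to this, because nothing on them records whether a response was seen again.

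**Working it through.** **Inputs from the protocol.** n = 20, single arm (Sections 2.3 and 6.1); two-sided 95% interval (Section 9.0); scans every two 4-week cycles (Schema, Section 5.1.3); median survival after relapse 4 to 5 months (Section 1.1).

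**1. The plan's own precision figure.** Section 9.0 promises "an interval that will extend no more than 0.21 from the observed response rate", with the condition "if we conservatively assume a response rate of 0.5 for calculations". The Wald half-width is 1.96 × √(0.5 × 0.5 / 20) = 0.219. At 10/20 the other intervals give 0.201 (Wilson), 0.207 (Jeffreys) and 0.228 (exact). The stated 0.21 is of the right order, and the protocol does not name the method. A confirmation rule changes neither n nor this figure.

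**2. Effect of one false responder.** 1/20 = 5 percentage points. Exact (Clopper-Pearson) 95% intervals:
- 0/20: upper limit 1 − 0.025^(1/20) = 16.8%, so 0 to 16.8%
- 1/20: lower limit 1 − 0.975^(1/20) = 0.13%, upper limit 24.9%
- 2/20: 1.2 to 31.7%

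**3. How many false responders?** The protocol gives no false-response probability. Purely as an illustration, assume a probability q per scan, independent between scans, and two scans per true non-responder. The chance of being credited is 1 − (1 − q)² on best recorded response and q² if both scans must agree.

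| q (assumed) | Credited, unconfirmed | Expected if all 20 are non-responders | Credited, confirmed |
|---|---|---|---|
| 1% | 1.99% | 0.40 | 0.01% |
| 5% | 9.75% | 1.95 | 0.25% |
| 10% | 19.0% | 3.8 | 1.0% |

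At q = 5%, the chance of at least one false responder among 20 is 1 − (1 − 0.0975)^20 = 0.87 unconfirmed and 1 − (1 − 0.0025)^20 = 0.05 confirmed. Correlated errors, for example from the same reader and the same lesions, would make confirmation less effective than this.

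**4. What confirmation would lose.** Assume exponential survival, S(t) = 0.5^(t/median), with 4.345 weeks per month.
- Week 8 (first scan): 72.7% alive with median 4 months, 77.5% with median 5.
- Week 16 (second scan): 52.8% and 60.0%.
- Alive at week 16 among those alive at week 8: 52.8/72.7 = 73% and 60.0/77.5 = 77%.

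So about 23% to 27% of patients alive at the first scan would die before the second, before counting other drop-out. Responders probably live longer than average, so for them this is more likely an upper guide.

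**The case against.** The strongest reply is that the protocol never says one scan suffices. It adopts RECIST 1.1 by citation, so any confirmation rule in that guideline could be said to enter with it, and the sentence quoted may only fix the time window. This stands in part: the text is silent and does not waive confirmation. But the protocol's own definition of its primary endpoint can then be read in two ways, and the forms record nothing that would support the stricter one.

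It is also fair that this is a descriptive pilot testing no hypothesis, that the intervals for 0/20 and 1/20 overlap heavily, and that confirmation carries its own downward bias in a population with short survival. That last point stands and shapes the remedy.

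A reader might go further and infer four things that the documents do not support:
- **The form makes the result something other than RECIST 1.1.** The protocol does not reproduce that guideline's rules on number of target lesions, nodal measurement or confirmation, so a departure cannot be shown from it.
- **Ten target rows admit false responders.** They are the form's capacity, not an instruction to measure ten lesions.
- **A nodal CR cannot be recorded.** The entry columns say only that a measurement is recorded, and response status has its own row, separate from the sum. Nor does the choice of diameter push one way: a node going from 30 × 20 to 20 × 15 mm changes by −33% in length and −25% in short axis, while 30 × 20 to 22 × 13 mm gives −27% and −35%.
- **The rule can only err upward.** True responses can be missed, and Section 5.1.3 itself says necrosis may make a lesion look larger.

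The Appendix D question about the treating physician's judgement concerns progression, so it is only indirect evidence on how response is read.

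**Conclusion.** The concern holds as a gap in the definition of the primary endpoint. Section 5.1.3 credits the best recorded response and states no requirement that it be seen again, so as written one unconfirmed reading counts. In this setting false-positive readings tend to inflate RR, by 5 points each. The total inflation is unknown: the illustrative 2% to 19% of true non-responders credited rests wholly on an assumed 1% to 10% false-response probability per scan, independence, and two scans per patient. The precision statement and the sample size are unaffected. This is a worthwhile and cheap improvement to a pilot estimate; it does not show that the planned RR would be wrong.

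**What to change.** In Section 5.1.3:
- Define confirmed RR as the percentage of patients whose CR or PR criteria are met again on the next scheduled scan, at least 4 weeks after the first.
- Report confirmed RR together with RR based on best recorded response, over the same patients, each with its 95% CI. Fixing both in advance prevents a choice between them once results are known.
- State how many responders had no later scan, so that absence of confirmation can be told apart from failure to confirm.

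In Appendix G, add an overall-response field for each assessment and a field for whether a CR or PR was confirmed and on what date. While revising the form, the sponsor should check its sum-of-LD line against the RECIST version cited in Section 5.1.3.

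The cost is wording and a revised form; the scans are already scheduled. The downside is that the confirmed rate may be noticeably lower: the next scan comes 8 weeks later, and some true responders will die or leave the study before it. Showing both rates lets the reader see the range between them.

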## 5.2 Specifics of Tests Performed During the Study

Described below are the specifics of the tests performed in this study.

### 5.2.1 ECOG Performance Status

The ECOG Performance Status scales (Oken et al 1982) will be used to assess how a patient's disease is progressing and assess how the disease affects the daily living abilities of the patient. These scales are listed in Table 5.2.1-1 (below). The higher the ECOG score, the worse the prognosis.

**Table 5.2.1-1: Scales Used in ECOG Performance Status**

| **Grade** | **ECOG** |
| --- | --- |
| 0 | Fully active, able to carry on all pre-disease performance without restriction |
| 1 | Restricted in physically strenuous activity but ambulatory and able to carry out work of a light or sedentary nature, e.g., light house work, office work |
| 2 | Ambulatory and capable of all self-care but unable to carry out any work activities. Up and about more than 50% of waking hours |
| 3 | Capable of only limited self-care, confined to bed or chair more than 50% of waking hours |
| 4 | Completely disabled. Cannot carry on any self-care. Totally confined to bed or chair |
| 5 | Dead |

### 5.2.2 Clinical Chemistry and Hematology

Clinical chemistry assessed includes:

| glucose | Ca^+2^ |
| --- | --- |
| creatinine | CO_2_ |
| total protein | BUN |
| albumin | AST/serum glutamic-oxaloacetic transaminase (SGOT) |
| Na^+^ | ALT/serum glutamic-myruvic transaminase (SGPT) |
| K^+^ | alkaline phosphatase (ALP) |
| Cl^-^ | total bilirubin |
| Mg |  |

Hematology assessed includes:

complete blood count with differential (platelet and hemoglobin included)

lactate dehydrogenase (LDH)

# 6.0 TREATMENT WITH CPI-613

CPI-613 will be administered to patients as shown in Table 6-1 (below). A treatment cycle is 4 weeks, with CPI-613 given on Days 1 and 4 of the first 3 weeks (i.e., 3-weeks-on-1-week-off). During each treatment cycle, patients will be treated with CPI-613 at the same dose, unless dose modification is warranted (see Section 6.2).

**Table 6-1: Administration of CPI-613 in Patients with Extensive Small Cell Lung Carcinoma**

| **Treatment Cycle** | | | **Administration of CPI-613** |
| --- | --- | --- | --- |
|  | **Week** | **Day** |  |
| **Cycle 1**  **(4 weeks)** | 1 | 1 | 2-hr IV infusion via a central venous catheter |
|  |  | 4 | 2-hr IV infusion via a central venous catheter |
|  | 2 | 1 | 2-hr IV infusion via a central venous catheter |
|  |  | 4 | 2-hr IV infusion via a central venous catheter |
|  | 3 | 1 | 2-hr IV infusion via a central venous catheter |
|  |  | 4 | 2-hr IV infusion via a central venous catheter |
|  | 4 |  |  |
| **Cycle 2**  **(4 weeks)** | 1 | 1 | 2-hr IV infusion via a central venous catheter |
|  |  | 4 | 2-hr IV infusion via a central venous catheter |
|  | 2 | 1 | 2-hr IV infusion via a central venous catheter |
|  |  | 4 | 2-hr IV infusion via a central venous catheter |
|  | 3 | 1 | 2-hr IV infusion via a central venous catheter |
|  |  | 4 | 2-hr IV infusion via a central venous catheter |
|  | 4 |  |  |
| Etc. until progression |  |  |  |

hr = hour; IV = intravenous; min = minutes.

## 6.1 Sample Size, Dose Levels and Justification of the Dose

The sample size will be 20 for this pilot trial.

This study will use the maximum tolerated dose (MTD) established in the study conducted by Pardee and colleagues (CCCWFU 29109; IRB00012124). This MTD for single-agent use of CPI-613 infused over 2 hours is 3,000 mg/m^2^.

## 6.2 Adverse Event-Related Dosing Delay and Dose Modification

For adverse events unrelated to serum creatinine elevation or reduction in renal function but are possibly related to CPI-613, the occurrence of Grade 1 toxicity does not generally require dose modification for subsequent doses for that patient. However, if Grade 2 toxicity (other than alopecia and nausea) probably related to CPI-613 develops, treatment is to be withheld and can resume only after the Grade 2 toxicity has been reduced to Grade 1 or below, and the dose level for subsequent doses for that patient will be reduced by 25% of the dose at which such Grade 2 toxicity occurs. Grade 2 alopecia and nausea do not require withholding treatment or dose reduction. If Grade 3 or 4 toxicity probably related to CPI-613 develops, dosing of CPI-613 of that patient will be withheld and the patient shall be monitored for recovery from, and reversibility of, such Grade 3 or 4 toxicity. To resume treatment with CPI-613 for a patient who has had CPI-613-related Grade 3 or 4 toxicity, the Grade 3 or 4 toxicity must be reduced to Grade 1 or below, and the dose level for subsequent doses for that patient will be reduced to 50% of the dose at which such Grade 3 or 4 toxicity occurs.

For adverse events related to creatinine elevation or reduction in renal function that are possibly related to CPI-613, dosing of the patient will be withheld if the severity level is Grade 1 or above. Treatment can resume only after the toxicity has been reduced to Grade 0. The dose level for subsequent doses for that patient will be reduced by 15% if the severity level is of Grade 1, by 25% for Grade 2 toxicity, and by 50% for Grade 3 or 4 toxicity.

Furthermore, if the toxicity possibly related to CPI-613 is acute renal failure and the severity level is Grade 3 or 4, further patient enrollment will be temporarily suspended in order to enable assessment of the following aspects of the trial and implementation of corrective measures or protocol amendment, and if necessary:

- compliance of the study sites and investigators to the study protocol

- evaluation of the appropriateness of the procedures for monitoring renal function

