## 6.3 Duration of Treatment for Each Patient at Each Cohort

Six months of treatment is recommended for patients who have a response, unless or until:

- Patients exhibit progression of disease together with worsening of biliary function, no longer meeting eligibility criteria, or exhibiting symptomatic progression; or patients exhibit progression of disease which was confirmed after 2 additional treatment cycles

- Unacceptable toxicity from CPI-613

- Patient withdrawal of consent

- Investigator’s discretion to withdraw patients from the study because continued participation in the study is not in the patient’s best interest.

- Undercurrent illness: a condition, injury, or disease unrelated to the intended disease for which the study is investigating, that renders continuing the treatment unsafe or regular follow-up impossible

- General or specific changes in the patient's condition that renders the patient ineligible for further investigational treatment

- Non-compliance with investigational treatment, protocol-required evaluations or follow-up visits

- Termination of the clinical trial by the sponsor

However, if therapy is considered beneficial according to the opinion of the treating physician, additional cycles of therapy may be given on the same treatment plan indefinitely up to the time of clear disease progression.

When terminating treatment during this trial, the investigator should make every effort to contact the patient and to perform a final evaluation. Also, the reason(s) for withdrawal from the study must be recorded.

Survival and post-study cancer treatment will be monitored via bi-monthly telephone contact once patients are removed from trial. All patients will be followed until death.

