# 8.0 ADVERSE EVENTS LIST AND REPORTING REQUIREMENTS

## 8.1 Adverse Event Characteristics

- **CTCAE term (AE description) and grade:** The CTEP Active Version of the NCI Common Terminology Criteria for Adverse Events (CTCAE 4.0) will be utilized for AE reporting.  The CTEP Active Version of the CTCAE is identified and located on the CTEP website at (<http://ctep.cancer.gov/protocolDevelopment/electronic_applications/ctc.htm>.  All appropriate treatment areas should have access to a copy of the CTEP Active Version of CTCAE.
- **‘Expectedness’**: AEs can be ‘Unexpected’ or ‘Expected’ (see Section 7.1 above) for expedited reporting purposes only.
- **Attribution** of the AE:
  - Definite – The AE *is clearly related* to the study treatment.
  - Probable – The AE *is likely related* to the study treatment.
  - Possible – The AE *may be related* to the study treatment.
  - Unlikely – The AE *is doubtfully related* to the study treatment.
  - Unrelated – The AE *is clearly NOT related* to the study treatment.

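### Section 6.2 mandates no dose hold for a non-renal Grade 3-4 event rated Possible, because the hold is tied to probably related toxicity

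*Protocol*

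**What the plan says.** Section 6.2 has one paragraph for non-renal adverse events and one for renal events.

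The non-renal paragraph opens with events that are unrelated to creatinine or renal function "but are possibly related to CPI-613, the occurrence of Grade 1 toxicity does not generally require dose modification". It then sets two hold rules, each with its own attribution condition:

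- Grade 2: "if Grade 2 toxicity (other than alopecia and nausea) probably related to CPI-613 develops", treatment is withheld until Grade 1 or below and then resumes at a dose reduced by 25%.
- Grade 3/4: "If Grade 3 or 4 toxicity probably related to CPI-613 develops, dosing of CPI-613 of that patient will be withheld".

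The resumption sentence follows directly: "To resume treatment with CPI-613 for a patient who has had CPI-613-related Grade 3 or 4 toxicity", the toxicity must first fall to Grade 1 or below, and later doses are 50% of the dose at which it occurred.

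The renal paragraph applies to possibly related events throughout. It holds dosing from Grade 1, requires recovery to Grade 0, and cuts the dose by 15%, 25% or 50% according to grade.

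Section 8.1 defines five attribution levels. Possible is worded as "The AE *may be related* to the study treatment", and Probable is a separate level meaning likely related. Section 6.0 sets the default within a cycle: "patients will be treated with CPI-613 at the same dose, unless dose modification is warranted (see Section 6.2"). Section 6.1 fixes the starting dose: "This MTD for single-agent use of CPI-613 infused over 2 hours is 3,000 mg/m^2".

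**The concern.** A dose-modification rule should tell the investigator what to do after every serious event that the drug may have caused. Here the paragraph is introduced at one attribution level and the Grade 3/4 action is set at a higher one. A severe or life-threatening non-renal event rated Possible falls between them, and the Section 6.0 default sends the reader back to the section that does not address it.

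What is at stake is patient safety and uniform dosing conduct. The trial doses at the maximum tolerated dose, in a population with prior chemotherapy and active disease, where it may often be hard to separate drug from disease as the cause. In that setting Possible is a plausible rating. One investigator may hold after such an event while another doses on schedule, and both would be within the protocol.

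**Working it through.** No stated figure needs to be reproduced. The check compares the rules by attribution level, then looks at how soon the next dose falls and whether another section supplies a hold.

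**1. Rules for a Grade 3 or 4 event, by attribution** (Section 6.2, with the Section 8.1 levels; *probably related* is read as a minimum, so that Definite is included)

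| Attribution | Non-renal Grade 3/4 | Renal Grade 3/4 |
| --- | --- | --- |
| Definite or Probable | hold; recover to Grade 1 or below; 50% of dose | hold; recover to Grade 0; reduce by 50% |
| Possible | no mandated hold | hold; recover to Grade 0; reduce by 50% |
| Unlikely or Unrelated | no rule | no rule |

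The empty place is the non-renal Possible cell. At Possible, even a renal Grade 1 event requires a hold, recovery to Grade 0 and a 15% reduction.

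**2. Time to the next infusion** (Table 5-1 and Table 6-1: Days 1 and 4 of Weeks 1 to 3, 4-week cycle)

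- Infusion days in the cycle: 1, 4, 8, 11, 15, 18. The next cycle starts on day 29.
- Gaps: 4 - 1 = 3; 8 - 4 = 4; 11 - 8 = 3; 15 - 11 = 4; 18 - 15 = 3; 29 - 18 = 11 days.
- After 5 of 6 infusions the next dose is therefore nominally due in 3 or 4 days. The footnotes to Table 5-1 let treatment move by one day either way.
- For a patient with no earlier reduction, that dose is 3,000 mg/m^2 (Section 6.1).

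**3. Does another section supply the hold?**

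- Section 6.3 lists unacceptable toxicity and the investigator's "discretion to withdraw patients from the study because continued participation in the study is not in the" patient's best interest. These are grounds for ending treatment. They carry no grade or attribution threshold and no recovery condition.
- Section 5.1.2 asks for symptoms and vital signs before each infusion, and for chemistry and hematology on Day 1 of Weeks 1 to 3. No dosing action is attached to a finding. A laboratory abnormality found on Day 1 has no scheduled repeat before the Day 4 infusion.
- Section 8.2 and Appendix B send unexpected Grade 4 and all Grade 5 events, whatever the attribution, to the Safety and Toxicity Review Committee, with notification within 24 hours. The committee may suspend the trial. Grade 3 events and expected Grade 4 events are not covered, and no patient-level hold is prescribed.

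None of these fills the empty cell.

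**The case against.** The strongest reply is that the threshold is deliberate. *Probably related* appears in both non-renal hold rules, while *possibly related* governs the renal rule, which is stricter throughout. That fits a planned gradation by organ risk. The *possibly related* phrase in the non-renal paragraph is also attached grammatically to the Grade 1 sentence, where no change is generally required. A low threshold for taking no action and a higher one for acting do not contradict each other.

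Much of this stands. The wording may be intended, and this is not an outright contradiction. The gap does not depend on how far the opening phrase reaches, however: even if it covers Grade 1 only, a non-renal Grade 3-4 event rated Possible still has no mandated hold. If that is intended, the protocol should say so.

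The safeguards also count. Discretion, pre-dose checks and committee review of unexpected Grade 4 events make it less likely that a patient is re-dosed through such an event. They narrow the concern without closing it.

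A reader might go further and infer two competing dose rules from the change to *CPI-613-related* in the resumption sentence: 3,000 mg/m^2 if Possible events are outside it, 1,500 mg/m^2 if they are inside. The text does not support building on that. A sentence about resuming presupposes a hold, and the only non-renal Grade 3/4 hold is the one just before it, so the phrase most naturally refers back to the *probably related* toxicity.

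**Conclusion.** The point holds as a cheap improvement. As written, Section 6.2 mandates no hold for a non-renal Grade 3 or 4 event rated Possible, although the next infusion is nominally 3 or 4 days away after five of six infusions and the renal rule acts at the same attribution from Grade 1.

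This rests on two assumptions: that *probably related* means at least Probable on the Section 8.1 scale, and that the investigator applies that scale when using Section 6.2.

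Its size in patients cannot be given, because the protocol states no expected rate of Grade 3-4 events or of Possible ratings.

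Three further inferences are not supported. The text does not direct re-treatment at full dose; it only fails to require a hold. The Grade 2 threshold is not shown to be wrong, since a higher attribution bar for a moderate event is a reasonable clinical choice. Nothing here affects the response rate, its precision statement in Section 9.0, or the toxicity summary by grade.

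**What to change.** Amend the two Grade 3/4 sentences of the non-renal paragraph in Section 6.2:

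- Apply the hold to toxicity that is possibly, probably or definitely related to CPI-613.
- Require recovery to Grade 1 or below before dosing resumes for all three levels.
- In the resumption sentence, replace *CPI-613-related* with explicit attribution levels. Keep the 50% reduction for probably or definitely related events, unless the clinical team decides to extend it to Possible.

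Leave the Grade 2 rule, including its alopecia and nausea exception, unchanged.

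This is a wording change with no effect on sample size or analysis. The downside is some additional holds, whose number cannot be derived from the document. There is a reason not to extend the 50% cut by default: Section 6.2 has no re-escalation rule, so each extra reduction would lower dose intensity in a pilot that Section 9.0 describes as 20 patients treated at the MTD. That trade-off belongs to the clinical team.
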